### Outcome measures

#### **
*Primary work outcomes*
**

The first primary outcome will be presenteeism, or at-work productivity, measured over 2 years, using the Work Instability Scale (WIS-RA) [36]. Developed for RA, the WIS measures mismatch between functional ability and work demands, and was designed to identify individuals at high risk of work loss warranting referral for vocational assessment. It has been shown to have good psychometric properties, including construct validity [37], and be effective at predicting future work transitions [38]. However, a drawback of the WIS is that it does not permit the calculation of associated costs. Therefore, for the purpose of the cost-utility analysis, at-work productivity will be measured using the Work Productivity and Activity Impairment – Specific Health Problem (WPAI-SHP) scale [39]. The WPAI-SHP measures overall impairment in activities (from work time missed, impairment while working, and activity impairment outside of work) due to a health problem, expressed as percent impairment, which can be used to calculate associated cost. Statistically significant improvement in both the WIS and the WPAI-SHP were observed in our pilot study.

The second primary outcome will be time to work cessation, measured over 5 years of follow up. Work cessation is defined as complete cessation of work for more than 6 months, the standard duration used by insurance companies to define permanent WD, and also consistent with definitions of WD in the employment literature [40]. This definition will capture WD from all health reasons (i.e. not only related to arthritis), including early retirement, work cessation for personal reasons, and prolonged unemployment periods when people are looking for another job, but will not capture temporary WD, sick leave, or short periods of unemployment of less than 6 months duration. Whether or not work cessation should be restricted to arthritis related work cessation is an issue of debate in the arthritis employment literature. Because of difficulties attributing work cessation to a single cause (i.e. the decision is often multifactorial and arthritis may have played some role in the decision), it is generally recommended that all-cause work cessation be measured in studies including a control group [41].

#### **
*Secondary work outcomes*
**

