### Sample size and analysis

Sample size was calculated for the primary outcome requiring the largest sample, i.e. time to work cessation. It was performed with PASS software [42] for time-to-event analyses. We assumed 5 years of follow-up and a rate of work cessation of 12.77% per year in the control group, based on the 40% work loss observed in controls over 4 years in Allaire’s RCT of VRC [34], and assuming an exponential distribution of time to work loss. A sample size of 420 subjects (210 per group) completing the study is necessary for 80% power, a 2-tailed Cox model-based score test, equivalent to the logrank test, at alpha = 0.05, to detect a 35% relative risk reduction (HR = 0.65) in the intervention vs. control group, which was considered a minimally clinically important difference (MCID), and is moderately conservative compared to the 42% risk reduction observed in Allaire’s study (HR = 0.58, 95% CI:0.34-0.99) [34]. Assuming 20% loss to follow-up, we will recruit a total of 526 subjects (263 per group). This sample will ensure adequate power for our other primary outcome, at-work productivity.

Appropriate descriptive statistics will be used to measure baseline characteristics of the two groups. Analysis of treatment effectiveness will rely on intention-to-treat (ITT) approach, so that all patients initially randomized will be included in the analysis, regardless of their compliance or drop-outs.

For the analysis of our first primary outcome, at-work productivity measured as a continuous variable will be tested for normality using the Shapiro-Wilk test [43]. If normality assumption is rejected, an appropriate transformation (e.g. such as logarithmic) will be employed to obtain an approximately normal distribution. Next, an Analysis of Variance (ANOVA) will evaluate the effect of the intervention on WIS measures at 2 years, adjusting for the 12 strata and blocking. We will also consider an Analysis of Covariance model after inspection of the baseline values in both treatment arms for factors such as WIS score, duration of disease, physician providing RA care, age, gender and risk factors for WD. If differences at baseline are observed, we will consider them as covariates. Since the power of these analyses will likely be less than the original ANOVA, post hoc power analyses will be conducted if these appear to be clinically meaningful adjustments.

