In the analysis of our second primary outcome, time-to-event (survival) methodology will compare the risk of work cessation in the intervention and control groups. Subjects employed until end of their follow-up (study end, death or time of loss to follow-up, whichever occurs earlier) will be censored. First, Kaplan Meier ‘survival curves’ and logrank test will estimate and compare the proportions of subjects who continue being employed in the intervention and control groups. Next, multivariable Cox Proportional Hazards (PH) regression model [44] will be employed to estimate the adjusted Hazard Ratio (HR) with 95% CI, associated with the intervention after controlling for potential risk factors for WD that may be imbalanced at baseline, despite randomization, and for other important predictors, such as age, gender, RA duration at baseline, and physician providing RA care, whose omission could induce bias toward the null in time-to-event analyses [45]. We will use a flexible extension of the Cox model [46], which will allow us to estimate how the HR reduction due to intervention changes over time, if the proportional hazard assumption (that the intervention effect remains constant over time) is rejected.

For analyses of secondary outcomes, time-to-event methods will be employed for dichotomous outcome variables (e.g. time to temporary work cessation), and comparison of means between intervention and control groups will be employed for continuous variables (e.g. measures of absenteeism, job satisfaction, self-efficacy and risk factors for WD), as described above for the primary outcomes.

For the second primary outcome (time to work cessation), an interim analysis will be performed at 2 years of follow-up. We will use the same method as for the primary analysis and will employ the PETO criteria to adjust the overall type I error for multiple testing [47]. Specifically, we will use a conservative type I error of 0.001 for the interim analysis, which will allow us to maximize the power of the final analyses of the 5 year outcomes, which will employ the conventional 0.05 significance level.

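### Baseline WIS should be named as a fixed covariate in the Cox model for work cessation: the protocol calls it a predictor of work transitions but leaves it off its list of example predictors

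*Protocol article*

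**What the plan says.** The Sample size and analysis section gives two routes into the Cox model for work cessation. One takes in work-disability risk factors that turn out unevenly distributed between the arms. The other takes in "other important predictors, such as age, gender, RA duration at baseline, and physician providing RA care, whose omission could induce bias toward the null" when the outcome is analysed as time to event. WIS is not named under either route.

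The Outcome measures section says that the WIS "was designed to identify individuals at high risk of work loss warranting referral for vocational assessment" and that it has been shown to "be effective at predicting future work transitions".

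For the productivity outcome, the Sample size and analysis section lists candidate covariates as "factors such as WIS score, duration of disease, physician providing RA care, age, gender and risk factors for WD". These are considered only after the baseline values have been inspected and differences seen. WIS stands there as an item separate from the risk factors for work disability. The work-related risk factors listed under Secondary work outcomes do not include it either.

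The two-year interim analysis of work cessation is to use the same method as the final analysis.

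**The concern.** The protocol's reason for adjusting beyond observed imbalance is sound: in a time-to-event model, omitting an important predictor moves the estimated hazard ratio toward 1 even when the arms are balanced. That reason applies to WIS at least as well as to age, gender, disease duration or treating physician. None of those four is described anywhere in the article as predicting work loss so directly.

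The two covariate lists in the same section are nearly the same, except that WIS is in the one for productivity and absent from the one for work cessation. If WIS did enter as a work-disability risk factor, it would come in only on observed imbalance, which misses the point of the protocol's own argument. Work cessation is the outcome on which the trial was sized, and a significant interim result on it would end the trial early. Its covariate set is therefore worth fixing before any data are seen.

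**Working it through.** **1. The plan's own figure.** The inputs, all from Sample size and analysis, are "a rate of work cessation of 12.77% per year in the control group", 5 years of follow-up, and a design "to detect a 35% relative risk reduction (HR = 0.65) in the intervention vs. control group", using "a 2-tailed Cox model-based score test, equivalent to the logrank test, at alpha = 0.05".

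- Hazard: −ln(0.6)/4 = 0.1277 per year, so the stated rate is an exponential hazard.
- Five-year event probability: control 1 − exp(−0.1277 × 5) = 0.472; intervention 1 − exp(−0.1277 × 0.65 × 5) = 0.340; mean 0.406.
- Schoenfeld events: 4 × (1.960 + 0.842)² / (ln 0.65)² = 169.2, rounded up to 170.
- Completers: 170 / 0.4058 = 419, against 420 stated. The Freedman formula gives 175 events and 431 completers, within 3%.
- Power at 420 completers (170.4 expected events): Φ(√170.4 × 0.4308/2 − 1.960) = 80.3%.
- Recruitment: 210 / 0.8 = 262.5, rounded up to 263 per group, or 526.

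The statement "A sample size of 420 subjects (210 per group) completing the study is necessary for 80% power" is therefore confirmed. No covariate enters the calculation.

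**2. What WIS would add.** The prognostic strength of WIS is not in the documents. I assumed a hazard ratio per SD of 1.0 to 2.5, beyond whatever the other covariates explain. The simulation used 4,000 trials per setting, 210 per arm and 5 years of follow-up. Baseline WIS was standard normal, and the treatment hazard ratio was 0.65 conditional on WIS. The baseline hazard was calibrated to 40% control work loss at 4 years. Each trial was fitted by Cox regression without and with WIS, using a two-sided Wald test at 0.05.

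| Assumed WIS HR per SD | Mean HR without / with WIS | Power without / with WIS |
|---|---|---|
| 1.0 | 0.650 / 0.649 | 78.3% / 78.3% |
| 1.25 | 0.652 / 0.649 | 79.1% / 79.5% |
| 1.5 | 0.661 / 0.648 | 76.4% / 79.6% |
| 2.0 | 0.678 / 0.647 | 70.6% / 79.6% |
| 2.5 | 0.703 / 0.652 | 62.0% / 78.4% |

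Monte Carlo error is about 0.7 points on each power. The simulated level without any WIS effect (78%) lies about 2 points below the formula's 80.3%, so compare within rows and not with the formula. A separate simulation gave 78% / 79%, 75% / 79% and 70% / 80% at 1.25, 1.5 and 2.0. Taken together, the gain is about 1 point or less, about 3 to 4 points, and about 9 to 10 points. At 2.5 it is about 16 points (78.4 − 62.0), but that is the far end of the assumed range.

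**3. At the recruited number.** With 526 enrolled and 20% lost over follow-up, power without / with WIS was 81% / 84% at 1.5, 80% / 85% at 1.75 and 78% / 85% at 2.0. A repeat run with exponential loss agreed within 1 point at 1.5 and 1.75, and gave 76% / 84% at 2.0.

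**The case against.** The strongest reply is that the list of predictors is introduced by such as. The commitment is to a class, important predictors, and WIS fits that class. The text does not exclude it, and a full covariate list is ordinary SAP content that this article need not carry. All of that stands, and the point should not be read as showing that WIS will be left out. What remains is that the only explicit rule for WIS in this document makes it conditional on observed imbalance, and that rule is written for the outcome that WIS itself measures. Unconditional inclusion for work cessation cannot be taken for granted.

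A reader might infer that the trial is underpowered. The documents do not support this. The stated 80% belongs to the unadjusted logrank test, and it reproduces. The simulation takes 0.65 as the effect conditional on WIS, so unadjusted power falls below plan by construction. If 0.65 is instead the unadjusted effect, as the sample-size calculation treats it, power without WIS is as planned and adjustment would add to it.

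A reader might also infer that the hazard ratio without WIS is invalid. It is not. The shift is the gap between a conditional and a marginal hazard ratio (non-collapsibility), and the logrank test keeps its type I error. Bias is the protocol's word for it.

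Finally, WIS may be a weaker predictor here than in the settings where it was studied. It was developed for rheumatoid arthritis, whereas this trial also enrols three other disease groups. Everyone enrolled already has concerns about work, which may narrow the range of scores. The endpoint counts cessation for any reason, including early retirement and unemployment. These are fair reasons to take the lower end of the assumed range seriously, and there the gain is negligible.

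**Conclusion.** The point holds as a recommended improvement and not as an error in the sample size or in the validity of the test. The protocol supplies both the principle (adjust for important predictors even without imbalance) and the case for WIS, but does not join them for the outcome on which the trial was sized.

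The benefit is confined to the adjusted Cox analysis; the planned logrank test is unaffected. At 420 completers it runs from negligible (hazard ratio 1.25 per SD) to about 9 to 10 power points (2.0). Over the same range, the hazard ratio without WIS goes from essentially unchanged to about 0.68, against a conditional 0.65. These sizes rest on an assumed strength of WIS beyond the other covariates, a normally distributed score, proportional hazards, and WIS actually being left out. The direction is secure; the size is not known from the documents.

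**What to change.** State in the analysis section, or confirm in the SAP, that baseline WIS enters the Cox model for work cessation as a continuous, prespecified covariate whether or not the arms differ on it. Use the same covariate set in the two-year interim Cox analysis. Say also that the adjusted hazard ratio is conditional on these covariates, so that it is not read as the same quantity as the unadjusted one.

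The cost is one model term. Baseline WIS is already among the baseline values that the analysts plan to inspect, and neither the sample size nor the logrank test needs to change.

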**Methods/Design:**

526 participants with IA will be recruited from British Columbia, Alberta, and Ontario in Canada. The intervention consists of a) 5 online group sessions; b) 5 web-based e-learning modules; c) consultations with an occupational therapist for an ergonomic work assessment and a vocational rehabilitation counselor. Questionnaires will be administered online at baseline and every 6 months to collect information about demographics, disease measures, costs, work-related risk factors for WD, quality of life, and work outcomes. Primary outcomes include at-work productivity and time to work cessation of > 6 months for any reason. Secondary outcomes include temporary work cessation, number of days missed from work per year, reduction in hours worked per week, quality adjusted life year for the cost utility analysis, and changes from baseline in employment risk factors. Analysis of Variance will evaluate the intervention’s effect on at-work productivity, and multivariable Cox regression models will estimate the risk of work cessation associated with the intervention after controlling for risk factors for WD and other important predictors imbalanced at baseline.

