## Methods/design

### Study design

Our study design is consistent with CONSORT recommendations for RCTs, 2010 update [32] and extension for trials of non-pharmacological treatments [33]. Participants will be stratified by location and arthritis type and randomized 1:1 to receive either our program, or “usual care” as initiated by their physician and supplemented by printed material about work and arthritis. Participants will be followed for 5 years, the estimated time required, according to our power calculations, to observe a difference in work cessation similar to that in Allaire’s RCT [34]. After 2 years, analysis of our first primary outcome, at-work productivity, will be performed, along with an interim analysis of the second primary outcome, work cessation. If a significant difference in work cessation is observed between the two groups, the RCT will be terminated prematurely. Because of the nature of the intervention, participants cannot be blinded. Ethics approval was obtained from the University of British Columbia Research Ethics Board (H11-03527).

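### Two primary outcomes are tested separately with no rule controlling error across them, and work cessation alone is given the full two-sided 0.05

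*Protocol article*

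**What the plan says.** The Abstract gives two primary outcomes: "Primary outcomes include at-work productivity and time to work cessation of > 6 months for any reason". Outcome measures numbers them: "The first primary outcome will be presenteeism, or at-work productivity, measured over 2 years, using the Work Instability Scale (WIS-RA"; and "The second primary outcome will be time to work cessation, measured over 5 years of follow up".

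They are analysed at different times. Under Study design: "After 2 years, analysis of our first primary outcome, at-work productivity, will be performed, along with an interim analysis of the second primary outcome". The same section ends the trial early if work cessation differs significantly at that point, without reference to the WIS result.

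Under Sample size and analysis, the WIS test is described only as follows: "an Analysis of Variance (ANOVA) will evaluate the effect of the intervention on WIS measures at 2 years". No significance level is attached to it. For work cessation the plan "will employ the PETO criteria to adjust the overall type I error for multiple testing". This sentence stands in a paragraph confined to the second primary outcome, and it is spelled out as two levels: "we will use a conservative type I error of 0.001 for the interim analysis", and then the "final analyses of the 5 year outcomes, which will employ the conventional 0.05 significance level". The sample size also uses two-sided alpha 0.05 on work cessation alone.

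**The concern.** The plan takes up overall type I error explicitly, but only for repeated looks at one of its two primary outcomes. That outcome then takes the whole 0.05. Nothing says how the WIS result and the work-cessation result combine into a conclusion about the program.

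The WIS result arrives three years before the final work-cessation analysis, in a trial whose participants are unblinded and report outcomes by self-administered questionnaire. A significant WIS result alone could be presented as primary evidence of effectiveness with no error budget behind it, and work cessation would then get a second chance at the full 0.05. A combining rule chosen after the 2-year WIS result is known would carry little weight.

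**Working it through.** **Inputs from the protocol article (Sample size and analysis, unless noted).** Work cessation: two-sided alpha 0.05, 80% power, HR 0.65, control hazard 0.1277 per year, 5 years, exponential, 420 completers, 20% loss, 526 recruited; 1:1 allocation (Study design). Interim at 2 years at 0.001, final at 0.05.

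**Assumptions, because the article does not state them.** WIS tested at two-sided 0.05 (lower levels also shown); either outcome alone suffices for a claim; correlation r between the two test statistics, shown over a range.

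**1. The plan's own figure.**
- Events (Schoenfeld): 4(1.960 + 0.842)² / (ln 0.65)² = 169.2, rounded up to 170.
- Five-year event probabilities: control 1 − exp(−0.1277 × 5) = 0.472; intervention 1 − exp(−0.65 × 0.1277 × 5) = 0.340; mean 0.406.
- N = 170 / 0.4058 = 419, against 420 stated. 210 / 0.8 = 262.5, so 263 per group and 526 in total.

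The sample size reproduces, and it confirms that the full 0.05 is spent on work cessation.

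**2. Family-wise error with both primaries at two-sided 0.05.**
- Independent: 1 − 0.95 × 0.95 = 0.0975.
- Correlated, 1 − P(|Z1| < 1.96, |Z2| < 1.96) from a bivariate normal:

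| r | 0 | 0.3 | 0.5 | 0.7 | 0.9 |
|---|---|---|---|---|---|
| Family-wise error | 0.0975 | 0.0951 | 0.0907 | 0.0835 | 0.0704 |

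**3. Only false positives that favour the program.** Each test then has 0.025: 1 − 0.975² = 0.0494 for independent tests and 0.0454 at r = 0.5, against 0.025 for one test.

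**4. Sensitivity to the unstated WIS level (independent tests, work cessation at 0.05).**
- WIS at 0.025: 1 − 0.975 × 0.95 = 0.074.
- WIS at 0.01: 1 − 0.99 × 0.95 = 0.060.

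**5. Contribution of the interim look.** The information fraction under the null is (1 − exp(−0.1277 × 2)) / (1 − exp(−0.1277 × 5)) = 0.225 / 0.472 = 0.48. With 0.001 at the interim and 0.05 at the end, work cessation alone has overall error 0.0503. The interim adds almost nothing; the excess comes from the second primary outcome.

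**6. Error and power under a remedy.** Power = Φ(2.8016 − z), where 2.8016 = 1.960 + 0.842 is the design's expected statistic at exactly 80% power.
- Alpha 0.04: Φ(2.8016 − 2.0537) = 0.773.
- Alpha 0.025 (equal split): Φ(2.8016 − 2.2414) = 0.712. Restoring 80% would need 205 events, 506 completers and about 633 recruited.
- Fallback error with WIS at 0.01 and work cessation at 0.04, independent tests: 1 − 0.99 × 0.96 = 0.0496; at most 0.01 + 0.04 = 0.05 under any correlation.

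**The case against.** The strongest reply is that the inflation rests on what the article does not say. It gives no WIS level and no combining rule, and multiplicity across primary outcomes is often set in an analysis plan, which is not shown here. It is also arguable that these are two separate claims, each reported at its own level. The objective names two effects, the economic analysis refers to work cessation as the trial's primary outcome, and Limitations presents preventing work disability as what matters most to funders. For work cessation alone the error is about 5%.

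Part of this stands, and it rules out three stronger readings that a reader might infer.
- *The false-positive rate is nearly doubled without qualification.* This needs WIS at 0.05, an either-outcome claim and low correlation. The article describes WIS as predictive of later work transitions, so positive correlation is plausible.
- *Any conventional test of WIS must take the error above 5% once work cessation has 0.05.* This is not so. A fixed sequence, or a rule that both must succeed, allows 0.05 on each main test without inflation.
- *A claim that the program works would carry a false-positive rate well above 5%.* The 9.75% counts errors in both directions. In favour of the program the rate is about 4.9%, which is double the nominal 2.5% but not above 5%.

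The appeal to a later analysis plan does not dispose of the point. The article already fixes 0.05 on work cessation and sizes the trial on it, so an alpha split would contradict it. It also ends the trial on work cessation alone at 2 years, which fits poorly with an unstated gate through WIS or a both-must-succeed rule. The joint wording of the objective lists aims; it does not state a success criterion.

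**Conclusion.** The concern holds in conditional form. Followed as written, the plan does not control error across its two primary outcomes; its only adjustment concerns repeated looks at one of them. The size is up to 9.75% two-sided against 5%, or about 4.9% against 2.5% in the direction of benefit. Both figures assume independent tests, WIS at two-sided 0.05 and a claim resting on either outcome. At correlations of 0.5 to 0.7 the two-sided figure is about 9.1% to 8.3%. A stricter WIS level reduces the excess but does not remove it while work cessation keeps an ungated 0.05. If both outcomes had to succeed, or a testing order applied, there would be no inflation from the main tests, but the article states neither.

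**What to change.** Before the 2-year analysis, write one procedure into the protocol or analysis plan that controls error across both primaries, and state the WIS level. Two workable forms:

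- **Fallback in calendar order.** Test WIS at 2 years at 0.01. Test work cessation at 0.04, rising to 0.05 if WIS was significant. Keep the 0.001 interim boundary, counted within the work-cessation level.
- **Fixed sequence.** Name one outcome primary and the other key secondary, tested only if the first succeeds. The rule in Study design that stops the trial on work cessation alone must be made consistent with the chosen order.

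Either is a wording change with no new data or recruitment. Under the fallback, work-cessation power falls from 80% to about 77% when WIS is not significant, and returns to 80% when it is. WIS faces a stricter level; the power cost of that cannot be computed, because the article gives no WIS effect size or standard deviation. The 0.01/0.04 split is one option, and the exact split is the sponsor's choice. An equal split would cost more, leaving about 71% power for work cessation at the planned size.

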### Data collection

Data will be collected on demographics, disease variables, co-morbidities, quality of life, costs, work-related risk factors for WD, and work outcomes, using a self-administered online questionnaire. Work outcomes, costs and quality of life will be assessed every 6 months, and other data once yearly. To evaluate co-interventions received in both groups, data will also be collected every 6 months about IA treatment received, “usual care” received from physicians and allied health professionals, information sought about employment issues, use of services specifically targeted at employment, and job accommodations made.

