We will also examine the incremental costs and benefits of receiving the intervention versus standard of care. Both a cost-effectiveness analysis and a cost-utility analysis will be performed. The outcome of our analysis will be the incremental cost-effectiveness ratio (ICER), which is the difference between the mean costs of providing competing interventions divided by the difference in effectiveness. Based on the primary outcome of the RCT, we will determine the incremental cost of the intervention per work cessation avoided relative to standard treatment. Because cost-effectiveness analyses are not robust to quantity or quality of life, we will also conduct a cost-utility analysis, where the primary outcome is the quality adjusted life year (QALY). Using health utilities measured by the EQ-5D and SF-6D, we will conduct a cost-utility analysis in which the incremental cost of the intervention relative to standard therapy per QALY gained will be determined. Important aspects of economic evaluations conducted alongside an RCT are excluding protocol driven costs, and dealing with missing data due to attrition. We will follow recommendations by the International Society for Pharmacoeconomics and Outcomes Research for missing cost and effectiveness data. We will use a combination of imputation and bootstrapping to quantify uncertainty due to missing values and finite study sample size. We will use propensity scores, stratified by treatment group, for imputing missing costs and effectiveness data due to attrition.

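### Imputing missing costs and effects from a dropout score makes weak use of each person's own history and, unless donors are limited to people still working at loss, overstates work cessation in the economic evaluation

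*Protocol article*

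**What the plan says.** The economic evaluation is the trial's second objective. Under *Sample size and analysis*, the Protocol article names its imputation method: "We will use propensity scores, stratified by treatment group, for imputing missing costs and effectiveness data due to attrition". Two general commitments come just before it: "We will follow recommendations by the International Society for Pharmacoeconomics and Outcomes Research for missing cost and effectiveness data" and "We will use a combination of imputation and bootstrapping to quantify uncertainty due to missing values and finite study sample size".

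Effectiveness has two meanings in that paragraph. In the cost-effectiveness analysis, which builds on the primary outcome, "we will determine the incremental cost of the intervention per work cessation avoided relative to standard treatment". In the cost-utility analysis it is the QALY, which *Secondary work outcomes* places at 2 years after the intervention.

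The clinical analysis of work cessation in the same section treats lost participants differently: "Subjects employed until end of their follow-up (study end, death or time of loss to follow-up, whichever occurs earlier) will be censored". *Data collection* shows what is known about a person before loss: "Work outcomes, costs and quality of life will be assessed every 6 months".

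The article does not say which variables enter the score, whether imputation goes wave by wave, how donors are chosen, or whether costs and effects are drawn together.

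**The concern.** A propensity score for missingness summarises who is likely to be lost. It is not built to predict what the lost person's cost, utility or work status would have been. Two people with the same score can have very different histories, so putting those histories into the score does not make it an outcome model. The 6-monthly work, cost and quality-of-life records are likely the best predictors of the missing values, and the named method uses them only indirectly.

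This matters most for the cost per cessation avoided. Someone known to be working when lost in year 3 has a much lower chance of stopping by year 5 than a randomly chosen participant, because three years of risk have already passed. Censoring uses that fact. A draw from people with a similar dropout score does not, unless donors are limited to those still working at the same time. One outcome could then carry two different 5-year rates in the same trial report, and the ratio's denominator would depend on how loss is split between arms.

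**Working it through.** **Inputs from *Sample size and analysis*:** 40% control work loss over 4 years, exponential times, HR 0.65, 5 years of follow-up, 80% power, two-sided alpha 0.05, 20% loss, 263 recruited per group. **Assumed:** loss is exponential and independent of cessation; donors are all participants whose 5-year status is observed, whatever their work history.

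**1. The plan's own figures.** Control hazard = −ln(0.60)/4 = 0.1277 per year; intervention hazard = 0.65 × 0.1277 = 0.0830. Five-year cessation = 1 − exp(−5 × 0.1277) = 47.2% and 1 − exp(−5 × 0.0830) = 34.0%, a difference of 13.2 points. Schoenfeld events = 4 × (1.960 + 0.842)² / ln(0.65)² = 169.2, so 170. The mean event probability is 0.4058, and 170/0.4058 = 419 against the stated 420. 210/0.8 = 262.5, so 263 per group and 526 in all. The inputs are coherent.

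**2. Where participants end up.** Loss hazard μ = −ln(0.80)/5 = 0.0446. With cessation hazard h:
- cessation observed = h/(h+μ) × [1 − exp(−5(h+μ))]
- completed while working = exp(−5(h+μ))
- lost while working = μ/(h+μ) × [1 − exp(−5(h+μ))]

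| | Control | Intervention |
|---|---|---|
| Cessation observed | 0.4280 | 0.3068 |
| Completed while working | 0.4225 | 0.5282 |
| Lost while working | 0.1496 | 0.1649 |
| True cessation by year 5 among the lost | (0.4719 − 0.4280)/0.1496 = 29% | (0.3397 − 0.3068)/0.1649 = 20% |
| Rate among donors | 0.4280/0.8505 = 50.3% | 0.3068/0.8350 = 36.7% |
| Arm total after imputation | 50.3% | 36.7% |
| True arm total | 47.2% | 34.0% |

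Of 263 per arm, about 39 and 43 are lost while working. The excess imputed cessations number about 8 (39 × 0.21) and 7 (43 × 0.17).

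**3. Effect on the difference.** With equal loss it is 50.3 − 36.7 = 13.6 points against 13.2. For a fixed incremental cost the ratio falls by about 3% (13.2/13.6 = 0.97).

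**4. Unequal loss (assumed splits, same formulas).**
- 25% control, 15% intervention: 51.3 − 36.0 = 15.3 points.
- 10% control, 25% intervention: 48.7 − 37.6 = 11.1 points.
- No true effect, 25% against 15%: 51.3 − 49.5 = 1.8 points, where the truth is 0.

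A different loss pattern (uniform loss times, with 20% per arm actually lost while working) gives 51.9% and 37.6%, a difference of 14.2 points. Its three unequal-loss results, with the percentages lost while working, are 16.9, 10.4 and 2.9 points.

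**5. Why the time of loss matters.** A control participant still working at loss has a remaining risk of 1 − exp(−0.1277 × (5 − t)): 40.0% if lost at 1 year, 31.8% at 2, 22.5% at 3 and 12.0% at 4, against 47.2% unconditionally.

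**6. Costs and QALYs.** In a simulated draw within propensity quintiles (assumed covariate effects, 24 to 26% lost), the cost-QALY correlation went from about −0.72 to −0.56 with separate donors and stayed at about −0.73 with a common donor. For QALYs at 2 years, the same loss hazard gives 1 − 0.8^(2/5) = 8.5% lost, not 20%.

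**The case against.** A reader might infer that the score ignores everything known about the person, including that they were still employed. The documents do not say so. Earlier work status, costs and utilities may well be in the score, and imputing wave by wave among those still working would largely remove the cessation error. A reader might also infer that the link between costs and QALYs is broken. That needs separate donors, which the text never mentions. Nor is it certain that the economic and clinical cessation figures will disagree: the article ties cessations avoided to the primary outcome, so using the survival estimate is compatible with its wording.

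The 50% and 37% are therefore an upper case. The ratio uses the difference, which moves by 0.4 points under equal loss, and the article states no unequal split. It also promises to follow a health-economics society's recommendations and to combine imputation with bootstrapping. Such details may be in the full protocol or analysis plan, which are not shown.

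All of that limits the size of the point. It does not remove it. The method is stated, not left open, and an analysis plan that follows the sentence inherits it. The general reference to recommendations does not displace the specific technique named after it, and bootstrapping measures uncertainty without correcting a poor imputation model. Participants cannot be blinded, and the *Control group* section offers controls the intervention at study end in order to limit loss. Unequal loss is therefore a plausible case, though its size here is an assumption.

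**Conclusion.** The point holds in a limited form. The named method uses prior data only through its relation to dropout. Applied to 5-year cessation with donors not restricted by work history, it inflates both arms by about 3 percentage points at 20% loss and departs from the censoring in the primary analysis. The difference is nearly unchanged with equal loss. It shifts by about 2 points in either direction under the assumed unequal splits, or by up to about 4 under the other loss pattern. These sizes rest on the assumed loss timing, independent loss and unrestricted donors.

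The effect on the 2-year QALY analysis is probably small, and weakening of the cost-QALY correlation is conditional on separate draws. The logrank and Cox analyses and the sample size are not affected. This is a worthwhile, inexpensive improvement to the economic evaluation, and it poses no threat to the primary conclusions.

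**What to change.** Replace the propensity-score sentence with two commitments.

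1. *Missing costs and utilities are imputed jointly, separately in each arm, by multiple imputation (for example chained equations with predictive mean matching). Predictors are each person's earlier costs and utilities, last known work status and the randomization strata. Imputation is combined with the planned bootstrap.*
2. *Cessations avoided are the difference between the arms' 5-year Kaplan-Meier estimates, re-estimated in each bootstrap sample together with costs.*

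The second commitment makes the cost-effectiveness ratio agree with the primary analysis. It relies on the same independent-censoring assumption as that analysis and adds no new one. Joint imputation within each bootstrap sample preserves the relation between costs and effects.

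The change costs some analysis-plan wording and modest extra programming. It needs no new data, because the predictors are already collected every 6 months or fixed at randomization. The specific gain from predictive mean matching was not simulated here; the case for it is that it models the missing values themselves.
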